## Methods

### Participants

To address these objectives two separate cohorts of 30–36 healthy adults who satisfy the inclusion/exclusion criteria outlined below will be recruited. One cohort will feature exclusively lean participants (body mass index (BMI) 20.5–25.0 kg/m^2^) and the other overweight/obese participants (BMI > 25.0 kg/m^2^). This will be confirmed using the fat mass index (FMI) obtained from a dual-energy x-ray absorptiometry (DEXA) scan, with values ≤ 7.5 kg/m^2^ and ≤ 11.0 kg/m^2^ classified as lean for males and females, respectively. In line with the objectives of this protocol the effects of IMF in these two cohorts will not be compared, instead they will be published as separate studies with matched methods to provide a thorough evaluation of the impacts of IMF in these two metabolically distinct populations.

Participants in each cohort shall then be allocated to one of three parallel intervention arms in a 1:1:1 allocation ratio using a stratified randomisation scheme. This will feature a factor for objectively measured physical activity level (PAL), which is calculated by dividing each participant’s total daily energy expenditure by their resting metabolic rate, to ensure an even distribution of lower activity (PAL < 1.75) and higher activity (PAL ≥ 1.75) participants in each condition. In accordance with best practice recommendations for randomised controlled trials [35], allocation concealment will be employed to minimise bias. The scheme will be generated by a senior author who is not involved in participant recruitment or management ([name]) using an electronic random number generator. Intervention allocation will be requested via email by those responsible for participant management (IT), with only the participant code, BMI/FMI and PAL being sent. As only the delivery team will engage with participants and know their corresponding code, whilst only the senior author knows the block sizes and sequences, it is not possible for the allocation to be reliably predicted or biased by either party. Full details of the overall randomisation scheme will be included in publications once all allocations are completed in order to prevent deciphering [36]. The protocol for these studies has received ethics approval from the National Health Service Research Ethics Committee (reference: 15/SW/0007) and has been registered at clinicaltrials.gov under reference number NCT02498002 (version: IMF-02, date: July 6, 2015).

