#### LAB 1 (baseline)

This initial lab session will provide a reference point for examining the stability of body mass, as an indicator of overall energy balance, throughout the ensuing 4-week monitoring phase in which habitual dietary intake and physical activity are quantified. In addition, this visit will serve to familiarise participants with key procedures to improve reliability over subsequent laboratory sessions [41, 42]. Specifically, this will involve the provision of a urine sample to measure hydration status before both height and body mass are measured. Resting metabolic rate and substrate oxidation will be quantified using indirect calorimetry of expired air samples, after which a fasted blood sample shall be drawn from the antecubital vein to measure baseline concentrations of certain biomarkers (e.g. glucose, cholesterol). To conclude this session, a supervised submaximal treadmill protocol will also be undertaken to individually calibrate the physical activity monitors being used throughout the study (Actiheart™).

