#### Intervention phase

During a 6-day rest following LAB 2, which is included to avoid prolonged periods of monitoring [46] and maintain the 4-week testing interval, participants will be randomised to one of the three parallel intervention arms outlined in Table 1. The three diet groups will last for 20 days each with transitions between 24-hour cycles occurring at 15:00 each day. Not only does this transition point allow the consumption of at least one main meal per day to aid motivation, but more importantly, it also ensures that the latter and more demanding part of the fast coincides with diurnal reductions in appetite to encourage adherence [47]. Furthermore, this structure still gives a full 24-hour fasting period, which is around double that achieved in most prior studies [8].

**Table 1 Tab1:** Intervention arms employed in the study protocol

Intervention	Description
Daily calorie restriction	Reduce normal intake by 25% every day
Intermittent fasting with calorie restriction	Alternate between 24-hour periods of fasting and feeding with 150% of normal intake on fed days
Intermittent fasting without calorie restriction	Alternate between 24-hour periods of fasting and feeding with 200% of normal intake on fed days

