### Data analysis

As outlined in the aims of the present study, the primary outcomes will explore the effects of the intervention on postprandial glucose/insulin responses (pre–post) and energy balance – reflected by changes in resting metabolic rate (pre–post), physical activity energy expenditure (monitoring–intervention) and postprandial thermogenesis (pre–post). Secondary outcomes will explore changes from pre- to post-intervention in body composition, substrate oxidation, lipid profile, leptin concentration, c-reactive protein concentration, adipose tissue gene expression, postprandial lipaemia and postprandial appetite regulation/perception. In addition, differences in physical activity intensity and dietary composition between the monitoring and intervention phases will be examined. As it is not the objective of this study to compare these differences between the cohorts, two sets of analyses will be conducted on a per protocol basis -– one for the lean cohort and one for the overweight/obese cohort. Both will centre upon a two-way mixed model analysis of variance featuring a factor for diet allocation and a factor for time-point. This will permit an examination of the effect of each diet on the outcomes of interest (i.e. pre vs. post/monitoring vs. intervention) and whether this effect varied between the three dietary conditions. Pre-existing differences between groups at baseline will be examined using a one-way analysis of variance featuring a factor for diet allocation. Significant differences emerging from these tests will be explored using appropriate post-hoc tests to adjust for multiple comparisons and isolate the source(s) of variance. In addition to these analyses at the group level, individual responses will also be closely scrutinised to examine whether outliers could be affecting the interpretation. Further analysis, such as sub-group analysis, may also be conducted in light of patterns emerging in the final dataset. Baseline characteristics of participants who withdraw during the intervention will also be compared against the final population using *t* tests. Statistical significance will be accepted at *P* < 0.05.

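### Each arm's pre-post change is labelled the effect of that diet although no arm keeps the habitual diet; causal claims should rest on the diet-by-time contrasts, with the run-in change in resting metabolic rate reported as supporting evidence on drift

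*Protocol article*

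**What the plan says.** Under Participants, each cohort is "allocated to one of three parallel intervention arms in a 1:1:1 allocation ratio". Table 1 lists daily calorie restriction and two intermittent fasting diets, one with and one without calorie restriction. No arm continues the habitual diet.

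The Data analysis section specifies a "two-way mixed model analysis of variance featuring a factor for diet allocation and a factor for time-point". It then says: "This will permit an examination of the effect of each diet on the outcomes of interest", glossed as pre versus post or monitoring versus intervention. The same sentence adds a second use, to see "whether this effect varied between the three dietary conditions". The energy-balance outcomes are "changes in resting metabolic rate (pre–post), physical activity energy expenditure (monitoring–intervention) and postprandial thermogenesis (pre–post".

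The Power calculation derives 9-11 participants per group for within-treatment effects in the primary outcomes and settles on 10-12.

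At LAB 1, "Resting metabolic rate and substrate oxidation will be quantified using indirect calorimetry of expired air samples", and these measurements are repeated fasted at LAB 2. Between the two visits come 4 weeks of habitual diet and activity, with body weight required to stay within 1.0 kg. One reason given for the 6-day rest after LAB 2 is to "maintain the 4-week testing interval", so the LAB 2-LAB 3 gap matches the run-in. LAB 1 also has a training role: "this visit will serve to familiarise participants with key procedures to improve reliability over subsequent laboratory sessions".

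**The concern.** A two-level time factor inside one arm cannot separate the diet from other things that change between two test days: residual habituation to the mouthpiece and the long test day, season, or regression to the mean. With no arm on the habitual diet, nothing inside the trial subtracts these from a within-arm change.

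This matters for two conclusions. Aim 1 opens by asking whether intermittent fasting elicits compensatory change at all, and only then compares it with daily restriction. The Discussion expects the eucaloric fasting arm to show whether changes are due to extended fasting alone. If resting metabolic rate fell to a similar degree in all three arms, the interaction would be null. The fall would then be read as compensation in every arm, including the eucaloric one, although non-diet drift would look the same.

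The trial already collects partial information on such drift for resting metabolic rate and fasting substrate oxidation, at both ends of the run-in. The stated analysis is pre-post only and gives that change no role.

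**Working it through.** **1. Reproducing the plan's sample size.** Inputs from the Power calculation: resting metabolic rate 1898 ± 262 before and 1670 ± 203 kcal/day after; 2-hour glucose 10.72 ± 3.56 before and 7.10 ± 2.96 mmol/L after; alpha 0.05 (two-tailed t test), power 80%. The pre-post correlation r is not given; r = 0.5 is assumed.

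SD of change = √(s₁² + s₂² − 2·r·s₁·s₂)

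- Resting metabolic rate: √(262² + 203² − 2·0.5·262·203) = 238 kcal/day. Standardised change = 228/238 = 0.958. The exact paired t test gives n = 11, as stated.
- Glucose: √(3.56² + 2.96² − 2·0.5·3.56·2.96) = 3.30 mmol/L. Standardised change = 3.62/3.30 = 1.097. This gives n = 9, as stated.
- An independent-samples t test gives 18 and 14 per arm and does not reproduce the figures.

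So the sizing is for a paired, within-arm test.

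**2. What a non-diet drift does to that test.** Drift is an assumption: 30, 50 or 75 kcal/day, which is 13%, 22% or 33% of the 228 kcal/day used for sizing. With no diet effect, the chance of P < 0.05 is the power of the two-sided paired t test at drift/SD of change:

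| Assumed drift (kcal/day) | r = 0.5, n = 10 | r = 0.5, n = 12 | r = 0.8, n = 12 |
|---|---|---|---|
| 0 | 5% | 5% | 5% |
| 30 | 6.5% | 6.9% | 9.3% |
| 50 | 9.2% | 10.2% | 17.2% |
| 75 | 14.5% | 17.0% | 32.6% |

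At r = 0.8 the SD of change is 157 kcal/day, so the same drift is easier to mistake for an effect. That r would not reproduce the plan's 11 (it gives 6).

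**3. Which contrasts are protected.** If drift δ is common to all arms, the observed change in arm k is (diet effect)ₖ + δ. The difference between arms j and k is (diet effect)ⱼ − (diet effect)ₖ, and δ drops out. Aim 2, aim 3 and the comparative half of aim 1 are differences of this kind. A single arm's change keeps δ.

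**4. What the run-in can and cannot supply.**

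- As a formal control within each arm, the contrast (LAB 3 − LAB 2) − (LAB 2 − LAB 1) is noisy. Assuming SDs 262, 262, 203 and equal correlations, its SD at r = 0.5 is 440 kcal/day. Detecting 228 then needs 32 per arm, and 10-12 gives 31-37% power. At r = 0.8 it needs 15 (62-72%), and at r = 0.9 it needs 9 (88-94%).
- Pooled over the cohort, the LAB 1-LAB 2 change has SD 262·√(2(1 − r)). The 95% half-width is t·SD/√n, with t = 2.045 at n = 30 and 2.030 at n = 36. At r = 0.5 (SD 262) this is ±98 and ±89 kcal/day; at r = 0.8 (SD 166), ±62 and ±56; at r = 0.9 (SD 117), ±44 and ±40.

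The pooled figure is therefore useful context, but not precise enough to act as a threshold unless r is high.

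**The case against.** The strongest reply is that the sentence on each diet's effect goes on to the randomised comparison between diets, where common drift cancels. Fasting with restriction against daily restriction isolates fasting at a matched deficit, and fasting with against without restriction isolates the deficit. Neither needs an untreated arm. This stands, and it limits the point to the first half of aim 1 and to stand-alone within-arm claims.

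Second, a reader might infer that the run-in goes to waste. The document does not support that. The monitoring phase is the comparator for physical activity energy expenditure, a primary outcome; it sets the intake targets and gates entry. LAB 1 also calibrates the activity monitors and provides baseline biomarkers. Only the LAB 1-LAB 2 change in the fasted measures lacks a role in the analysis.

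Third, familiarisation at LAB 1 and averaging of agreeing samples from three collections are mitigations. They reduce the expected drift. Nothing in the document shows that they remove it, and they do not address season or regression to the mean.

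Fourth, a reader might want a rule that a within-arm change counts only if it exceeds the run-in change. That goes too far. LAB 1-LAB 2 contains the first-exposure effect that LAB 2-LAB 3 was arranged to avoid, and the formal contrast is underpowered at r = 0.5. Body mass cannot be benchmarked at all, because its run-in change is held under 1.0 kg by design.

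Fifth, a supporting analysis of LAB 1 data is commonly left to a fuller plan. That is fair for the extra analysis. It does not cover the causal label on within-arm change, which the article states itself.

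**Conclusion.** The point holds in a limited form. The plan labels each arm's pre-post change as that diet's effect and sizes the trial on it, although no arm continues the habitual diet. Such a change is uncontrolled and cannot by itself show that intermittent fasting causes compensation, or that fasting alone explains a change in the eucaloric arm. The between-diet conclusions are not affected by drift common to the arms.

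The size is conditional. The 6-17% range rests on r = 0.5 and on a drift of 30-75 kcal/day; the document gives neither the drift nor its direction. The range shows how sensitive the within-arm test would be, and is not evidence that drift occurs.

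**What to change.** In the Data analysis section:

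1. State that causal conclusions about the diets rest on the diet-by-time contrasts.
2. Describe within-arm pre-post changes as uncontrolled, and word the first half of aim 1 and the eucaloric-arm claim accordingly.
3. For resting metabolic rate and fasting substrate oxidation, and any fasting biomarker actually assayed at both LAB 1 and LAB 2, report the LAB 1-LAB 2 change pooled over arms within each cohort, with its 95% confidence interval, beside each arm's LAB 2-LAB 3 change. Present it as a supporting estimate of non-diet drift, not as a pass/fail gate, and do not apply it to body mass.

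The cost is wording and one further summary from data already collected. The limits should be stated with it: first-exposure familiarisation may make LAB 1-LAB 2 overstate later drift; the interval may differ for participants who repeat the monitoring phase; and postprandial glucose, insulin and thermogenesis are not covered, because test meals are given only at LAB 2 and LAB 3.

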## Discussion

Despite the growing popularity of IMF [55], research exploring its effects on human metabolism remains scarce. The novel examination of postprandial responses and the components of energy balance being employed in this study will highlight the extent to which IMF regimes can impact human metabolism. The isocaloric contrast of IMF and daily calorie restriction will also add a further dimension by thoroughly benchmarking IMF against current nutritional strategies for improving metabolic health. Furthermore, the inclusion of a eucaloric IMF arm will examine whether any observed changes can be attributed to extended fasting alone as opposed to chronic energy imbalance. Finally, in exploring all of these facets in both lean and overweight/obese groups, the present study will also clarify the effect of baseline adiposity on observed changes, which may unravel the discrepancies seen in prior studies [56, 57]. Taken together, this approach will help to provide clearer and more informed public health messages on the safety and efficacy of such diets relative to conventional approaches.

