Secondly, reductions in fasting insulin concentration have been consistently shown in response to various IMF interventions as reviewed by Barnosky et al. [8]. This review also highlights that, in a subset of these studies, fasted indices of insulin resistance generally improve following a period of IMF. However, it is important to note that these fasted measurements can often overlook subtle modifications in glucose metabolism under dynamic conditions [27] such as those seen in the postprandial period. At present there is a dearth of knowledge on how IMF impacts postprandial metabolism which needs to be addressed, especially upon considering that Western cultures spend the majority of their waking time in a postprandial state [28]. Furthermore, discerning the relative contributions of fasting and negative energy balance to any observed changes in metabolism carries substantial implications for how obesity and the associated comorbidities are treated, as it has been suggested that temporal modifications in energy intake exert independent influences on metabolic health [29–32].

With over 50% of the adult population in the UK currently classified as overweight or obese [33], accompanied by an increased risk of type 2 diabetes and cardiovascular disease, finding more effective strategies to manage these conditions remains imperative [34]. Although the limited body of prior literature offers promising insights as to the efficacy of IMF in improving metabolic health, numerous uncertainties remain. As such, the present study has three core objectives that will be separately addressed in both a lean cohort and in an overweight/obese cohort.

The study will aim (1) to establish whether IMF elicits compensatory changes in the components of energy balance and compare these against the changes arising from a daily calorie restriction intervention; (2) to examine the effect of IMF on postprandial metabolism relative to a daily calorie restriction intervention; and (3) to explore whether IMF impacts upon postprandial metabolism and the components of energy balance independently from chronic energy imbalance by contrasting against a eucaloric IMF intervention.

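### The Discussion promises to clarify the effect of baseline adiposity, but the planned analyses exclude any comparison of the lean and overweight/obese cohorts

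*Protocol article*

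**What the plan says.** Three places in the protocol article keep the cohorts apart.

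- Background sets out "three core objectives that will be separately addressed in both a lean cohort and in an overweight/obese cohort".
- Methods, Participants: "the effects of IMF in these two cohorts will not be compared, instead they will be published as separate studies with matched methods".
- Methods, Data analysis: "As it is not the objective of this study to compare these differences between the cohorts, two sets of analyses will be conducted". Each set centres on a "two-way mixed model analysis of variance featuring a factor for diet allocation and a factor for time-point". Neither cohort nor a measure of adiposity is a term in the model.

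The Power calculation section follows the same line. It sizes each arm for within-treatment change and keeps the two populations separate.

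The Discussion then claims, as a benefit of studying both groups, that "the present study will also clarify the effect of baseline adiposity on observed changes", and adds that this may help to explain discrepancies among prior studies.

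The Data analysis section also leaves room for unplanned work: "Further analysis, such as sub-group analysis, may also be conducted in light of patterns emerging in the final dataset".

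**The concern.** To say how baseline adiposity affects the changes, one must compare changes between people of differing adiposity. In this design that is a cohort-by-time difference (the change differs between cohorts whatever the diet) or a cohort-by-diet-by-time difference (the contrast between diets differs between cohorts). Two separate diet-by-time analyses provide neither as an output.

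At stake is a conclusion that the article announces with no analysis behind it. The Discussion goes on to link the overall approach to public health messages, so the claim may be carried into the results papers. There, two sets of tests judged at P < 0.05 make it easy to treat significance in one cohort and non-significance in the other as a difference between cohorts. That pattern does not test a difference.

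**Working it through.** **1. The text.** The Participants and Data analysis sections exclude the between-cohort comparison. The Discussion claims a result that only such a comparison can give. The optional further analysis does not reconcile them: it depends on patterns seen in the final data, names no cohort comparison, and would conflict with the Participants section if used for one. This step needs no arithmetic and settles the point.

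**2. Reproducing the protocol's sample sizes.** Inputs from the Power calculation section: resting metabolic rate 1898 ± 262 to 1670 ± 203 kcal/day (change 228); 2-hour glucose 10.72 ± 3.56 to 7.10 ± 2.96 mmol/L (change 3.62); two-sided alpha 0.05; 80% power. The pre-post correlation r is not given, so I assume 0.5.

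SD of change = √(s₁² + s₂² − 2·r·s₁·s₂)

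- Resting metabolic rate: √(262² + 203² − 262 × 203) = 238.05; standardised change 228/238.05 = 0.958; exact paired t test gives n = 11.
- Glucose: √(3.56² + 2.96² − 3.56 × 2.96) = 3.30; standardised change 3.62/3.30 = 1.097; n = 9.

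Both match the stated 11 and 9. Treating pre and post as independent groups gives 18 and 14 per group, which does not match. The stated sizes therefore cover a pre-post change within one arm and nothing between cohorts.

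**3. How often equal cohorts would disagree.** For two independent cohorts with the same true effect and power p each, the probability that exactly one is significant is 2p(1 − p). At the stated within-treatment power of 80%: 2 × 0.8 × 0.2 = 0.32. (Both significant: 0.64; neither: 0.04.)

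**4. What a direct comparison could detect.** The contrast is the difference between cohorts in the difference between two diets, on change scores: SE = SD × √(4/n), with 6n − 6 degrees of freedom and n = 10-12 per arm in each cohort. At r = 0.5:

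| Cohort-by-diet difference | Resting metabolic rate: power | n per arm per cohort for 80% | Glucose: power | n per arm per cohort for 80% |
|---|---|---|---|---|
| As large as the whole assumed effect | 32-37% | 35 | 40-47% | 27 |
| Half of it | 12-13% | 138 | 14-16% | 105 |

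Over r = 0.3 to 0.8, power for the whole effect runs from about 25% to 70% (resting metabolic rate) and 30% to 82% (glucose). For half of it, the ranges are 10% to 24% and 11% to 30%. The ends of that range of r do not reproduce the protocol's sample sizes (14 and 12 at r = 0.3; 6 and 5 at r = 0.8).

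For a cohort difference in change within a single diet arm, power at r = 0.5 is 53-61% and 64-73% for the whole effect, and 17-20% and 21-25% for half of it. A cohort-by-time difference averaged over all three diets has SE = SD × √(2/(3n)), smaller than that of the cohort-by-diet contrast by a factor of √6 ≈ 2.4, but it averages over diets that the trial expects may act differently.

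**The case against.** The best defence is that the analysis plan is consistent with itself. Background, Participants, Power calculation and Data analysis all keep the cohorts apart on purpose. The conflicting sentence is a statement of rationale in the Discussion, not an objective, outcome or planned test, and its remark about prior discrepancies is hedged. No design or sample-size decision rests on it. This stands as a limit on how serious the point is. It does not remove the contradiction, because the adiposity clause itself is unqualified.

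Two stronger readings are tempting and are not supported.

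- A reader might infer that comparing P values is the only way the authors could reach an adiposity statement, so that false adiposity effects will follow. The protocol nowhere plans that comparison. Separate analyses also yield estimates and standard errors, which can be set side by side or differenced as independent estimates, and the Data management section commits to releasing the anonymised dataset. The narrower statement is the true one: no planned analysis estimates or tests the effect.
- A reader might infer that the cohorts would disagree on significance about half the time. Figures of 48-50% need a power of 50-60% per cohort (2 × 0.6 × 0.4 = 0.48; 2 × 0.5 × 0.5 = 0.50). The protocol states only 80%, for within-treatment change, which gives 32%. The higher figure is an assumption, and either figure does harm only if the disagreement is interpreted.

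It can also be said that an added interaction analysis would be too imprecise to clarify much. That is fair, and is why removing the claim is the simpler remedy.

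**Conclusion.** The point holds. The Discussion announces a conclusion about baseline adiposity that the stated analyses cannot support, because they exclude the comparison it requires. This follows from the text alone. The within-cohort analyses and the three objectives are unaffected.

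The figures are illustrative. The 32% assumes equal true effects, independent cohorts and the stated 80% power in each. The power figures for a direct comparison assume r = 0.5, which the document does not give but which reproduces its sample sizes, and a between-cohort difference expressed as a fraction of the effects used for sizing. They show that a direct comparison could be exploratory only.

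**What to change.** Choose one.

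1. **Withdraw the claim.** Delete the adiposity clause in the Discussion, or limit it to describing the effects in each cohort separately. Add to Data analysis that a result significant in one cohort and not in the other will not be read as an effect of adiposity. Cost: two sentences.

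2. **Keep the aim and analyse it.** Amend the Participants and Data analysis sections to allow one analysis of both cohorts, labelled exploratory, that reports the cohort-by-time and cohort-by-diet-by-time differences with 95% confidence intervals. State that cohort is not randomised, so a difference cannot be attributed to adiposity alone, and that precision is low. Soften the Discussion verb to match. Cost: one additional model. The methods are matched across cohorts, so no new data are needed.

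Recruitment was still open according to Trial status, and the Data management section gives the route for protocol modifications.
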